## 4. Study outcomes

A list of substantial adverse events in bariatric surgery (tabl 2) was predefined before study start. Possible occurrence of any of these will be identified in the CRF (SOREg) but additionally from the national quality health care registries (listed above) during 5-years of follow-up. A superiority of SG over GBP would require >35% fewer patients experiencing one or more substantial adverse event.

Time to occurrence of first substantial adverse event will be analysed as the co-primary outcome. Patients will be defined as either having or not having an event, and thus the number of events in the same patients will not be summarized.

For non-inferiority, weight loss difference over 5-years in patients operated with SG as compared to GBP will be evaluated with regards to the non-inferiority margin of 5%.

Table 1: Primary outcomes:

| Outcome                    | Time frame                  | Explanation                                                                          |
|----------------------------|-----------------------------|--------------------------------------------------------------------------------------|
| Weight loss                | At 5 years after surgery    | Change in weight from baseline in % of total body weight                             |
| Substantial adverse events | Over 5 years after surgery. | Number of patients with any substantial adverse events defined according to table 2. |

Table 2: Substantial adverse events: (events that may have a significant and/or longstanding effect on patients' health and/or everyday life).

| Substantial adverse event              |                                                                                                                                                                                                                                                                                               |
|----------------------------------------|-----------------------------------------------------------------------------------------------------------------------------------------------------------------------------------------------------------------------------------------------------------------------------------------------|

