### 5.1 Sample size and power

153

154 The sample size calculation is based on evaluation of the primary objectives. For evaluation of  
 155 superiority, it is assumed that 13% of patients who undergo GBP will have substantial adverse events  
 156 (as defined in the Study outcomes) over 5 years. It is further assumed that this risk is 35% lower in  
 157 patients in the SG group. Based on these assumptions, it is estimated that a total of 2100 patients  
 158 (1050 in each group) will be required to detect a difference in time to substantial adverse event with  
 159 >90% power at two-sided 2.5% significance level using Cox proportional hazards regression model.

160 Initially the power calculation was based on a SAE rate of 5% over 5 years, leading to the need to  
 161 include 4000 patients (especially regarding subgroup analysis). Partly due to slower than expected  
 162 inclusion rate, but mainly based on data suggesting more events of substantial adverse events than  
 163 expected (i.e., 13%) the sample size was recalculated to n=2100 to obtain sufficient power.

164 This sample size will also have 90% power to evaluate non-inferiority of 5 % weight loss difference  
 165 over 5 years between the two groups, assuming 15 kg standard deviation in weight loss over follow-  
 166 up with two-sided 2.5% significance level.

167

168 See appendix for an updated, post hoc, power-calculation before the closure of the trial inclusion.

169

170 

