### 5.2 Principles of analysis

171

172 The primary conclusions from this study will be based on analyses conducted under the principle of  
 173 intention-to-treat. Thus, all randomised patients, with exception to those who withdraw their  
 174 consent, will be included in the analyses. In the analysis, it is further assumed that all randomised  
 175 patients receive the treatment they were randomised to.

Those patients who are randomised but withdraw their consent to use their data will not be included in any analyses. Only the information that they were enrolled into the study and withdrew their consent, and the original treatment group to which they were allocated, will be reported.

Data from all operating clinics (centres) will be pooled in primary analyses. The study will be conducted under a common protocol for each participating clinic with the intention to pool the data for analyses.

In addition to the primary analysis using intention-to-treat population, exploratory analyses using per-protocol (as treated) populations will be conducted for all outcome variables.

For primary outcomes, two-sided 2.5% significance level will be used to identify statistically significant results. The corresponding confidence intervals to be reported will be 97.5% confidence intervals. The use of 2.5% significance is due to two primary endpoints.

There will not be any formal interim analyses on primary outcomes. The safety and Data Monitoring Committee has a responsibility to monitor adverse events and complications during the study follow-up period.

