### 5.3 Statistical analyses

Summary tables (descriptive statistics and frequency tables) will be provided for all baseline variables, outcome variables, and safety variables, as appropriate. Continuous variables will be summarized with descriptive statistics (n, mean, standard deviation, range, and median). Frequency counts and percentage of subjects within each category will be provided for categorical data.

Incidence of substantial adverse events will be analysed with time-to-event models. Time to first substantial adverse event (as defined in chapter 4 Study outcomes) from primary surgery will be recorded. Kaplan-Meier estimates of cumulative incidence of adverse events will be calculated in both treatment groups. Treatment effect will be calculated as a hazard ratio, together with corresponding confidence interval and p-value for the test of equal hazard ratio, from Cox proportional hazard regression model. The proportionality assumption of the Cox models will be evaluated graphically using "log-log" plots.

The primary conclusions will be based on a model which includes study centre as a covariate together with indicator for treatment. Explorative analyses will be conducted using sex, age, body mass index, smoking and diabetes at baseline as covariates.

For non-inferiority, the difference in weight loss between treatment groups and its confidence interval will be calculated and evaluated against the non-inferiority margin of 5%. The weight loss difference at 5-year follow-up will be estimated with a multilevel mixed-effect regression models utilizing body weight measurements at all available time points. This model takes into account the repeated measurements nested within persons over time. All randomized patients except those who have withdrawn their consent will be included in this analysis, independent of availability of body weight data during the follow-up. The primary conclusions will be based on a model which includes study center in addition to indicator for treatment.

For secondary outcomes, incidence of comorbidities during the follow-up will be evaluated with time-to-event models, and for continuous variables mixed-effect regression models will be used to evaluate differences between the treatment groups.

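### SAP section 4 states a >35% reduction as a requirement for superiority on substantial adverse events, which conflicts with the Cox test against no difference in sections 2, 5.2 and 5.3 and with the use of 35% as the assumed effect in section 5.1

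*Combined protocol and SAP*

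**What the plan says.** All references are to the main SAP (version 5) unless noted.

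- **Section 4, Study outcomes:** "A superiority of SG over GBP would require >35% fewer patients experiencing one or more substantial adverse event". The sentence does not say whether the 35% applies to the estimate, to a confidence limit or to the true effect.
- **Section 2, Study objectives:** the superiority hypothesis is that SG patients have fewer adverse events over 5 years. No minimum reduction is given. The protocol's primary outcome section also gives none.
- **Section 5.1, Sample size and power:** "it is assumed that 13% of patients who undergo GBP will have substantial adverse events" over 5 years, and "It is further assumed that this risk is 35% lower in" the SG group. With 1050 per group the plan claims ">90% power at two-sided 2.5% significance level using Cox proportional hazards regression model".
- **Section 5.2, Principles of analysis:** "For primary outcomes, two-sided 2.5% significance level will be used to identify statistically significant results".
- **Section 5.3, Statistical analyses:** the treatment effect is a hazard ratio, reported with its "corresponding confidence interval and p-value for the test of equal hazard ratio, from Cox proportional hazard regression model". Primary conclusions come from the model with study centre and treatment.
- **Appendix:** the post hoc calculation again assumes a 35% lower rate (25% against 16.25%) and reports 87.5% power at 413 per group. Inclusion stopped at 1752 patients.

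**The concern.** The same 35% appears in two roles. In section 5.1 it is the true effect under which the trial should have a high chance of a significant result. In section 4 it is worded as a condition for claiming superiority. A planning effect and a success threshold are different things, and a trial powered for the first is not powered for the second.

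The two rules also sit on different scales: section 4 speaks of patients with an event, sections 5.2 and 5.3 of a hazard ratio. That difference is small here, because censoring is at a fixed 5 years and register coverage is expected to be close to complete.

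At stake is the conclusion on a co-primary outcome. If the observed reduction is significant but smaller than 35%, the SAP supports opposite conclusions. The choice between them would be made after the result is known, and either choice could be challenged by citing the SAP against itself.

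**Working it through.** **Inputs.** 13% and 35% lower (8.45%), 1050 per arm, two-sided 2.5% (section 5.1). 25% and 16.25%, 413 per arm (Appendix). 1752 included, taken as 876 per arm (Appendix total; the equal split is my assumption). Full 5-year follow-up and no centre adjustment are assumed throughout.

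**Step 1: the plan's own power.** Schoenfeld's formula with hazard ratio 0.65:

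events = 4 × (2.2414 + 1.2816)² / (ln 0.65)² = 4 × 12.41 / 0.1856 ≈ 268.

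268 / 0.13 = 2062 patients, close to 2100. With 2100 × 0.13 = 273 events, power is 90.6%. The stated >90% is therefore reproduced, as the power of a test of hazard ratio 1. It uses 13% in both arms. With 13% against 8.45% there are about 225 events, and power is 83.9% (hazard ratio 0.65) or 88.1% (0.634, the hazard ratio implied by the two risks, ln 0.9155 / ln 0.87). The 87.5% in the Appendix reproduces as a comparison of two proportions at two-sided 5% (87.6%); at two-sided 2.5% it is 80.8%. Neither figure includes a 35% threshold.

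**Step 2: chance of meeting section 4 read literally.** The log of the observed risk ratio is roughly normal around the true value, with

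SE = √[(1−p₁)/(n·p₁) + (1−p₂)/(n·p₂)].

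If the true risk ratio is 0.65, P(observed < 0.65) = Φ[(ln 0.65 − ln 0.65)/SE] = Φ(0) = 0.50. SE cancels, so sample size does not matter. Exact binomial calculation gives 50.1% in all three scenarios.

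**Step 3: compare with the 2.5% test.** Power on the log risk ratio scale is Φ(0.4308/SE − 2.2414). For 13% against 8.45% and n = 1050, SE = √(0.00637 + 0.01032) = 0.129 and power = Φ(1.09) = 86%. Other standard methods for the same two risks give up to 88%. The smallest significant observed reduction comes from the pooled two-proportion z-test with the GBP rate fixed. For example, at 13% and n = 1050 with risk ratio 0.76: z = 0.0312 / √(0.1144 × 0.8856 × 2/1050) = 2.246, just above 2.2414.

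| Scenario | SE | Meets >35% at true 35% | Test power at true 35% | Smallest significant observed reduction | At true 30%: meets >35% / test significant |
|---|---|---|---|---|---|
| 13%, 1050 per arm | 0.129 | 50% | 86–88% | 24% | 28% / 73% |
| 25%, 413 per arm | 0.141 | 50% | 80–82% | 26% | 30% / 66% |
| 25%, 876 per arm | 0.096 | 50% | 99% | 18% | 22% / 95% |

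The last column is from simulation with the pooled z-test.

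**Step 4: variants of the threshold.**
- Requiring >35% and p < 0.025 together: still about 50% in each scenario, because an observed reduction above 35% is already significant.
- Threshold placed on the hazard ratio (below 0.65), at 225 events: 50% if the true hazard ratio is 0.65, 57% if it is 0.634.
- Confidence limit required to exclude a risk ratio of 0.65: about 1.2% at a true 35% reduction.
- True reduction needed for a 90% chance of an observed reduction above 35%: about 45% at 13% and 1050 per arm; about 43% at 25% and 876 per arm, from exp(ln 0.65 − 1.2816 × 0.0965) = 0.574.

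**The case against.** The strongest reply is that the working rule is already clear. The objectives, the significance level, the model, the null hypothesis and the basis for primary conclusions all point to a test against no difference, and section 5.1 labels the 35% as assumed. The sentence in section 4 stands in the outcome definitions, not in the statistical methods, and may simply be planning language that was carried over. This is plausible, and it limits what can be claimed. A reader might infer that the SAP has adopted a threshold on the observed estimate and that the trial therefore has only 50% power. The documents do not support that: the sentence names no estimate or confidence limit, and the 50% follows from the literal reading alone. What the reply does not remove is the conflict. The words state a requirement, and nothing in the SAP withdraws or explains it.

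A second reply concerns size. A reader might infer that any reduction of 20–35% would be clearly significant and yet fail section 4. That is not general. An observed 20% reduction is not significant under the planned inputs or the Appendix inputs, and at 876 per arm with 25% events it only just passes. The range of disagreement has to be given by scenario.

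A third reply is that a demanding bar for clinical relevance may have been intended. The documents do not exclude this, so the fix must allow for it.

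**Conclusion.** The concern holds as an internal conflict over the decision rule for a co-primary outcome. Section 4 states a requirement of more than 35% fewer patients with an event; sections 2, 5.2 and 5.3 contain no such requirement, and section 5.1 uses 35% only as an assumption.

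The two rules disagree for observed reductions from about 24% to 35% in the planned design, 26% to 35% in the Appendix scenario, and 18% to 35% at 876 per arm with 25% events. On the literal reading, the chance of success at the design effect is about 50%, against roughly 80–99% for the test across these scenarios. The stated >90% and 87.5% therefore do not describe the section 4 rule.

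These sizes assume an equal split of the 1752, full follow-up and unadjusted comparisons. That the two rules conflict rests on the text alone and needs none of these assumptions. Whether the sponsor would apply section 4 literally cannot be determined from the documents.

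**What to change.** By a dated SAP amendment, made before comparative 5-year results are seen, replace the section 4 sentence with: *Superiority of SG is concluded if the upper limit of the two-sided 97.5% CI for the hazard ratio (SG vs GBP) from the centre-adjusted Cox model is below 1; the 35% reduction is the planning assumption only.* Report the 5-year Kaplan-Meier risk difference and risk ratio with confidence intervals as well, so that readers can judge the size of the effect.

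If a 35% threshold was intended, the SAP must instead state its scale (proportions or hazard ratio), whether it applies to the estimate or to a confidence limit, and the power for that rule.

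The cost is one sentence, with no new data or patients. The amendment should record its reason and what data had been seen. If the sentence was meant as a criterion, dropping it lowers the bar after recruitment closed and after two-year trial data had been used in the Appendix calculation.

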## Background

Laparoscopic Roux-en-Y gastric bypass (RYGB) has in recent years been the standard operation in Swedish bariatric surgery. The operation is well studied and we have a good idea of the expected result regarding weight, BMI, comorbidities, and it can be performed with a low complication rate. However, this does not mean that the surgical method is without challenges, and above all there is a small but important group of patients with prolonged morbidity after the procedure. Due to the bypassing of the duodenum and proximal jejunum, there is also a concern for long-term risk of various types of deficiency conditions.

Laparoscopic sleeve gastrectomy (SG) is a relatively recently introduced surgical method that in recent years has gained rapid and wide spread internationally and is currently the most commonly used obesity surgical technique in the United States. However, there are not results from long-term studies to the same extent as for RYGB. However, the reported data indicate good results regarding weight development and resolution of comorbidity up to a few years after the operation, although to a somewhat lesser extent compared to after RYGB. There are currently no long-term data presented for SG.

RYGB has been associated with a non-negligible risk of internal herniation with small bowel obstruction, which appears to affect at least 10% of patients operated on without closure of mesenteric defects, and despite closure a risk remains. This risk of internal herniation does not exist with SG. Another advantage of SG is that it avoids the problems with the Jejunojejunostomy (JJ), which seems to be part of the rare but difficult to treat morbidity after RYGB. There is also probably a slightly lower risk of vitamin and mineral deficiency because the duodenum and proximal jejunum are not bypassed. However, there are data that suggest that problems with gastro-oesophageal reflux may occur or worsen after SG and that continuous acid-suppressing treatment may be necessary. There are also indications that revisional surgery rates may be higher after SG, e.g. due to unsatisfactory weight development over time.

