## **Secondary outcome measures**

Secondary outcome measures include health economics, inpatient care, outpatient care, drug consumption, alcohol abuse, fractures, diabetes, cancer, mortality and quality of life. Secondary outcome measures are described in greater detail in the statistical analysis plan.

As a comparative measure of quality of life, patients will complete the EQ5D-5L, SF-36 and OP quality of life questionnaires at baseline, as well as at 1 year, 2 years and 5 years. In Norway, the validated quality of life questionnaires WRSM, IQOQOL, HADS, GSRS and GERDQ are also filled in. To look at quality of life related to alcohol, we also want to follow/analyze AUDIT and B-Peth, where those parameters are available.

The physical examinations (abdominal circumference, etc.) that are done and blood samples that are taken in the study at 1- and 2-year controls should take place in the time interval -1 month to +3 months around the target date. For the 5-year check-up, the time interval  $\pm$  6 months around the target date is accepted.

For data verification and completion, information regarding the bariatric surgery and background information can be retrieved from medical records.

The mandatory analyzes are vitamin D, P-Glucose and HbA1c. In Norway, a standard set of blood samples is taken in addition to the mandatory analyzes in SOReg.

We are planning subgroup analyzes regarding sex, age (18–29; 30–45; >45 years), BMI (<42 and >42kg/m^2 respectively, which is the median BMI in SOReg) and +/- type 2 diabetes.

Subgroup analysis regarding gallstone intervention is planned.

In addition to the clinical follow-up, we will, with the help of coordination between SOReg and other national registers (Medicines register (2005-), Patient register (inpatient care 1987-, Outpatient care 2001-); The Cancer Registry, Intensive Care Registry, National Diabetes Registry, Försäkringskassan's MiDAS register, the Swedish Tax Agency and other relevant national registers), get a good picture of the effect, safety and cost-effectiveness of each surgical method over a long follow-up period. In Norway, the corresponding national registers will be used (the Cancer Register, the Cause of Death Register, the Prescription Register, NPR data and data from Statistisk Sentralbyrå).

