### Exclusion criteria:

- The patient is deemed not suitable for surgery with either method according to the surgeon's assessment or the clinic's routine
- Ongoing substance abuse. (Requires documented drug abstinence according to the clinic's routines, but minimum 1 year)
- Unstable psychiatric illness or other known contraindication to bariatric surgery .
- Previously undergone bariatric surgery or antireflux surgery.
- Moderate-severe reflux disease. (Not symptom-free on PPI in a dose equivalent to 20mg Omeprazole/day, and/or volume reflux, or presence of glandular metaplasia (Barrett's oesophagus)) or known hiatal hernia >4 cm
- Planned other simultaneous significant surgery, e.g. cholecystectomy.
- Inflammatory bowel disease

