|----------------------------------------------|-----------------------------|-----------------------------------------------------------------------------------------------------------------------------|
| Arterial cardiovascular events               | Baseline, 1, 2, and 5 years | Number of patients with Composite outcome including myocardial infarction, stroke and/or other occlusive arterial condition |
| Venous event                                 | Baseline, 1, 2, and 5 years | Number of patients with composite outcome including deep vein thrombosis, pulmonary emboli, and/or other venous events      |
| Diabetes requiring pharmacological treatment | Baseline, 1, 2, and 5 years | Development of diabetes measured as numbers of patients having a diabetes                                                   |

|                                                     |                             |                                                                                                                                  |
|-----------------------------------------------------|-----------------------------|----------------------------------------------------------------------------------------------------------------------------------|
|                                                     |                             | diagnosis with oral and/or injection treatment                                                                                   |
| Psychiatric morbidity                               | Baseline, 1, 2, and 5 years | Number of patients with pharmacological treatment for a psychiatric diagnosis                                                    |
| Hypertension                                        | 1, 2, and 5 years           | Number of patients with pharmacological treatment for                                                                            |
| Malignancy                                          | Baseline, 1, 2, and 5 years | Number of patients diagnosed with any type of malignancy
Data collected from Cancer registry                                  |
| Dyslipidaemia                                       | Baseline, 1, 2, and 5 years | Number of patients with oral lipid lowering treatment                                                                            |

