| Mineral nutritional status                          | 2 and 5 years               | Serum concentrations of iron depots, zinc, magnesium, selenium and copper, where available.                                      |
| Vitamin nutritional status                          | 2 and 5 years               | Serum concentrations of vitamins (vitamin B12, vitamin D, vitamin A and thiamine), where available.                              |
| Serum concentrations of albumin                     | 2 and 5 years               | Serum albumin, where available.                                                                                                  |
| Quality of Life                                     | Baseline, 1, 2, and 5 years | EQ-5D, Obesity Problems (OP) and SF-36 scores                                                                                    |
| Alcohol consumption                                 | 1, 2, and 5 years           | Alcohol consumption assessed by AUDIT, where available.                                                                          |
| Gastro-esophageal reflux disease                    | 1, 2, and 5 years           | Gastro-esophageal reflux disease is defined as present if symptoms of GERD are reported with or without relief by PPI treatment. |
| Fractures                                           | 2 and 5 years               | Diagnosis of any fracture collected from clinical data and national registry                                                     |
| Mortality and cause of death                        | 5, 10, (20 and 30) years    | National Cause of Death registry                                                                                                 |
| Health care consumption and cost-effective analysis | 5, 10, (20 and 30) years    | Data from in-hospital registry (days in hospital), Outpatient registry (number of visits), and National drug registry (type      |

|                        |                          |                                                                                                                                                 |
|------------------------|--------------------------|-------------------------------------------------------------------------------------------------------------------------------------------------|

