| PPI treatment for dyspepsia?                     | Y/N                                                                                                              |
| Depression                                       | Current diagnosis and/or medication                                                                              |
| Experiencing muscle/skeletal pain                | Y/N                                                                                                              |
| Prior Deep Vein Thrombosis or Pulmonary Embolism | Y/N                                                                                                              |
| Smoking                                          | Non-smoker, Current smoker, Temporary smoking cessation in conjunction with current surgery, Former smoker       |

119

120 Table 2: Surgical Data

|                                               |                                                                                                             |
|-----------------------------------------------|-------------------------------------------------------------------------------------------------------------|
| Surgical Data                          |                                                                                                             |
| Operating hospital                            |                                                                                                             |
| Surgical access                               | Laparoscopic/Open                                                                                           |
| Conversion from laparoscopic to open surgery? | Conversion because of: large liver; bleeding; equipment problems; adhesions; port placement problems; short |

|                                                                                         |                                                                                                           |
|-----------------------------------------------------------------------------------------|-----------------------------------------------------------------------------------------------------------|
|                                                                                         | mesentery; for other reasons                                                                              |

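### The secondary GERD outcome counts PPI-relieved reflux without reference to baseline, although patients with PPI-controlled reflux can enter, so new, persistent and relieved reflux cannot be told apart

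*Combined protocol and SAP*

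**What the plan says.** **Outcome.** The secondary outcomes table in SAP v5, section 4, says: "Gastro-esophageal reflux disease is defined as present if symptoms of GERD are reported with or without relief by PPI treatment". Its time frame is 1, 2 and 5 years. Most comorbidity rows in that table (arterial and venous events, diabetes, psychiatric morbidity, malignancy, dyslipidaemia) instead read "Baseline, 1, 2, and 5 years".

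**Entry.** The protocol's exclusion criteria define moderate to severe reflux as "Not symptom-free on PPI in a dose equivalent to 20mg Omeprazole/day, and/or volume reflux", or Barrett's oesophagus, and also exclude a known hiatal hernia above 4 cm. Milder reflux that a PPI controls does not exclude a patient.

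**Analysis.** SAP v5, section 5.3: "For secondary outcomes, incidence of comorbidities during the follow-up will be evaluated with time-to-event models". Mixed models are named for continuous variables. The exploratory covariates are sex, age, BMI, smoking and diabetes; the subgroups are sex, age, diabetes and BMI. Neither list has a reflux or PPI term.

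**Baseline data.** Table 1 of the perioperative analysis plan records "PPI treatment for dyspepsia" as yes or no. SAP v5, section 3.4, links the Prescribed Drug Registry and the corresponding Norwegian registries. For Norway, the protocol's section on secondary outcome measures adds that "GSRS and GERDQ are also filled in". The plan ties none of these to the GERD outcome.

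**The concern.** The protocol's Background raises the concern that "problems with gastro-oesophageal reflux may occur or worsen after SG". An outcome that answers this has to separate reflux that began or worsened after surgery from reflux that was there before and did not change. This one does not. A patient with PPI-relieved reflux before surgery and the same PPI-relieved reflux at the 1-year visit meets the definition. In an incidence model with no rule for existing disease, that patient is an event at the first visit.

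Reflux is one of the disadvantages the protocol expects of SG, and the GERD figure is likely to be read as a guide to choosing an operation. One merged figure would combine new onset with persistence and, if either operation relieves existing reflux, with relief as well. A reader could recover none of the three from it.

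**Working it through.** The plan states no rate, sample size or power for this outcome, so there is no figure to reproduce. The check has a textual part and an illustration on assumed rates.

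**Textual part**

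1. Entry admits reflux that is symptom-free on a PPI at the stated dose.
2. The outcome counts reflux symptoms whether or not a PPI relieves them. The admitted reflux is therefore a subset of what the outcome counts.
3. The row requires no new onset, no worsening and no comparison with baseline.
4. GERD is yes/no. Of the two methods in section 5.3 for secondary outcomes, only the incidence time-to-event model fits it. No rule sets aside patients who already have the condition.
5. The planned covariates and subgroups do not supply the missing baseline status.

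**Illustration**

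Assumptions, none from the documents: baseline PPI-controlled reflux *b* of 5 to 15%, equal in both arms through randomisation; new GERD of 20% (SG) and 8% (GBP) among the rest, a ratio of 2.5. Let *r* be the share of baseline reflux that persists.

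Reported GERD = *b* × *r* + (1 − *b*) × new-GERD rate.

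Full persistence in both arms (*r* = 1):

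| *b* | SG | GBP | Ratio | Difference |
|---|---|---|---|---|
| 0% | 20.0% | 8.0% | 2.50 | 12.0 points |
| 5% | 0.05 + 0.95 × 0.20 = 24.0% | 0.05 + 0.95 × 0.08 = 12.6% | 1.90 | 11.4 points |
| 10% | 0.10 + 0.90 × 0.20 = 28.0% | 0.10 + 0.90 × 0.08 = 17.2% | 1.63 | 10.8 points |
| 15% | 0.15 + 0.85 × 0.20 = 32.0% | 0.15 + 0.85 × 0.08 = 21.8% | 1.47 | 10.2 points |

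Now let GBP relieve existing reflux while it persists after SG, at *b* = 15% (SG stays at 32.0%):

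- GBP relieves half: 0.15 × 0.5 + 0.85 × 0.08 = 14.3%; ratio 32.0/14.3 = 2.2.
- GBP relieves all: 0 + 0.85 × 0.08 = 6.8%; ratio 32.0/6.8 = 4.7.

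The merged ratio equals 2.5 when 2.5 × (*b* × *r* + (1 − *b*) × 0.08) = *b* + (1 − *b*) × 0.20. The new-GERD terms cancel, leaving *r* = 1/2.5 = 0.4 at any *b*. On these assumptions the merged figure understates the ratio for new GERD if GBP relieves less than 60% of existing reflux, and overstates it if GBP relieves more.

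**Second illustration, with a smaller effect**

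Assume new GERD of 10% (GBP) and 15% (SG), ratio 1.50; full persistence; 1752/2 = 876 patients per arm with no losses; two-sided 5% test. The last column assumes that baseline reflux is identified without error.

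| *b* | Reported GBP vs SG | Ratio | Pre-existing share, GBP / SG | Power, all patients | Power, new GERD in reflux-free patients |
|---|---|---|---|---|---|
| 5% | 14.5% vs 19.3% | 1.33 | 34% / 26% | 76% | 87% |
| 10% | 19.0% vs 23.5% | 1.24 | 53% / 43% | 63% | 85% |
| 15% | 23.5% vs 27.7% | 1.18 | 64% / 54% | 53% | 83% |
| 20% | 28.0% vs 32.0% | 1.14 | 71% / 62% | 45% | 81% |

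**The case against.** **The outcome may be meant as prevalence.** The row speaks of GERD being present at a visit, whereas the diabetes row speaks of development, and section 5.3 does not name GERD among the comorbidities. On that reading the burden of GERD at each visit is a legitimate quantity, and randomisation balances pre-operative reflux on average. This stands: the all-patient prevalence comparison is valid. But the plan then names no method for it, and new and persistent reflux still cannot be separated.

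**Serious reflux is handled elsewhere.** The co-primary Severe GERD item requires symptoms that medication cannot control, or Barrett's with an endoscopy before surgery showing none. Because entry excludes reflux that the stated PPI treatment does not control, that item mostly captures worsening. Revision surgery counts as an event with its indication documented, and 5-year gastroscopy is planned with separate consent. This also stands, and it confines the point to the secondary outcome.

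**Baseline information exists.** A reader might infer from the time-frame column that no baseline reflux information is collected. The documents do not support this. The hypertension row omits baseline too, yet the perioperative plan records antihypertensive treatment at baseline, and it records PPI use for dyspepsia as well. The gap is that the outcome does not use this information.

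**The numbers are assumed.** True, and the direction of distortion depends on how far each operation relieves existing reflux. Under full persistence the absolute difference moves little: from 12.0 to 11.4 or 10.2 points.

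**A later plan can settle it.** The protocol foresees separate analysis plans for each publication. That offers a place for the fix but does not remove the need for it.

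**Conclusion.** The point holds for one secondary outcome. The definition counts PPI-relieved reflux with no reference to baseline, the entry criteria admit such reflux, and the only method in section 5.3 that fits a yes/no outcome would count it as an event if unchanged.

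Three stronger readings go too far. The between-arm comparison is not biased by this, because baseline reflux is balanced on average. The relative effect is not necessarily diluted: on the assumed 20% vs 8%, the ratio of 2.5 becomes 1.9 (5% baseline reflux) or 1.5 (15%) under full persistence, but 4.7 at 15% if GBP relieves all existing reflux. And the outcome does not match the admitted reflux one for one; it also counts unrelieved symptoms and reflux at any PPI dose.

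All sizes rest on assumed baseline prevalence, new-onset rates and persistence. No primary conclusion is affected.

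**What to change.** Amend SAP v5, section 4, or the plan for the 5-year publication, before the GERD data are analysed by arm:

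1. Add baseline as a time point for GERD. Take reflux status from the baseline item on PPI for dyspepsia, supplemented by pre-operative PPI dispensing in the linked drug registers and, in Norway, by GERDQ and GSRS if they were completed at baseline. Fix the dispensing window in advance and end it before surgery, since the protocol prescribes a PPI to every patient postoperatively.
2. Report GERD prevalence at 1, 2 and 5 years in all patients, adjusted for baseline status, and name the model.
3. Restrict any incidence analysis to patients without baseline reflux.
4. Among patients with baseline reflux, tabulate persistence or relief by arm.

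**Cost.** SAP wording and two further tables. No new data collection is needed, provided that the register extracts cover the pre-operative period.

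**Downside.** PPI use for dyspepsia is an imperfect marker of reflux. Untreated baseline reflux will be missed and may later appear as new, so the new-GERD figure should be labelled as conditional on the marker.
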